### 2.6. Data Collection and Follow-Up

The members of the study team prospectively gather data. During the baseline visit (T = 0), they collect historical data (demographic, laboratory—including parameters like hemoglobin, eGFR, and liver function—and clinical characteristics, including medication usage) from available medical records or through patient interviews if records are unavailable.

Primary and secondary endpoints are recorded at both 3-month and 1-year follow-up. The 3-month follow-up is conducted via telephone interview. Laboratory results are noted to the extent available within routine clinical practice, without performing additional study-related laboratory analyses. Patients are queried about adverse events, side effects of rivaroxaban, and any changes in their antithrombotic regimen (e.g., temporary cessation of aspirin, rivaroxaban, or both) and other medications. The time of final data collection is at one year, either through a face-to-face visit or via telephone contact (±30 days), or at 30 days in case of an early discontinuation of rivaroxaban therapy.

Potential reasons for premature study termination include consent withdrawal, loss to follow-up, or death of the patient. At this final observation, the patient’s condition and treatment assessment will be documented.

The treating physician determines the actual duration of treatment, which is not contingent on the initially intended treatment duration. In patients who permanently discontinue the combined treatment, discontinue rivaroxaban alone, or discontinue aspirin alone and who do not withdraw consent or experience a fatal adverse event during the observational period, the treating physician collects information on their survival status at the end of the study (i.e., 1-year ± 30 days after study inclusion).

A more detailed description of the variables collected during these visits is found in Table 3.

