### 2.5. Study Endpoints

The primary effectiveness endpoint is a composite of the following events at one year:Major adverse cardiac events (MACEs; composite of cardiovascular death, myocardial infarction (MI), or stroke);Clinically driven coronary, peripheral, or carotid revascularization;Stent thrombosis.

Clinically driven revascularization is defined as a de novo hospital admission that leads to revascularization (excluding planned or staged procedures). Definite or probable stent thrombosis is defined according to the Academic Research Consortium (ARC) criteria [16]. Myocardial infarction is defined according to the fourth universal MI criteria [17].

The primary safety endpoint is major bleeding during one year. These major bleeding complications are analyzed according to the International Society on Thrombosis and Haemostasis (ISTH) criteria as a composite of (1) fatal bleeding, (2) symptomatic bleeding into a critical organ (such as intracranial, intraspinal, intraocular, retroperitoneal, intra-articular or pericardial, or intramuscular with compartment syndrome), or (3) bleeding causing a fall in hemoglobin level of 2 g/dL (1.24 mmol/L) or more or leading to transfusion of two or more units of whole blood or red cells [18]. In addition, all bleeding events, including minor bleedings according to ISTH definitions, will be reported.

Secondary endpoints will be the following:Occurrence (and date) of stroke.Occurrence (and date) of MI.Occurrence (and date) of cardiovascular death.Occurrence (and date) of coronary revascularization procedures (PCI, CABG).Occurrence (and date) of peripheral revascularization procedures.Occurrence (and date) of carotid revascularization procedures.Occurrence (and date) of minor bleeding complications according to ISTH (clinically relevant bleeding that does not meet criteria for major bleeding and that requires any medical or surgical intervention to treat the bleeding).

A detailed overview of the primary endpoints is provided in Table 2.

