### 2.8. Data Analysis

All statistical analyses were performed using IBM SPSS Statistics, version 28.0 (IBM Corp., Armonk, NY, USA).

The statistical analyses are explorative and descriptive. All analyses are performed for the total study population (overall analyses). The study period for analyses is defined as the time from the start of rivaroxaban until the end of the 1-year follow-up.

Descriptive statistics are performed for both primary and secondary study parameters. Continuous variables are expressed as mean ± standard deviation and as medians with minimum, maximum, 25th, and 75th percentiles. Categorical variables are presented by frequency tables (absolute and relative frequencies). Incidence proportions are computed together with corresponding exact 95% confidence intervals (CIs) for primary and secondary endpoints. Cumulative incidence of events or survival probabilities and 95% confidence intervals are estimated using Kaplan–Meier estimates for primary and secondary endpoints. The follow-up starts per definition on the date of the start of treatment and ends at the date of a first event, date of loss to follow-up, or date of end of the one-year study period, whichever comes first. The incidence of events over time is studied with the use of Kaplan–Meier methods. Patients who do not experience an event of interest by the end of their individual observation period are censored.

To control for confounding, the primary analyses will employ multivariable Cox proportional hazards regression models, with adjustment for prespecified baseline covariates known to influence clinical outcomes: age, sex, presence of diabetes mellitus, renal function, and CHA_2_DS_2_-VASc score. Model assumptions, including proportional hazards, will be assessed using Schoenfeld residuals. In addition, propensity score methods will be implemented as sensitivity analyses to further address confounding and potential selection bias. Propensity scores will be estimated using logistic regression models including the aforementioned covariates. These scores will be incorporated via adjustment for the propensity score as a covariate in the Cox model.

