Missing data will be categorized by cause (e.g., treatment discontinuation, withdrawal of consent, or loss to follow-up) and described in detail. For time-to-event analyses (e.g., Kaplan–Meier estimation), patients will be right-censored at the date of last contact if no event has occurred. Dropouts due to reasons unrelated to outcome (e.g., relocation or administrative issues) will be assumed non-informative.

For other outcome measures, complete-case analysis will be the primary analytic approach. In addition, we will perform sensitivity analyses using multiple imputation under the assumption of missing at random, where appropriate. This approach allows us to explore the robustness of our findings and assess potential bias due to missing data. The dropout rate and its potential effect on external validity will be reported and discussed as part of the study limitations.

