Assessment of antithrombotic therapy	X	X	X
Assessment of clinical outcomes		X	X
End of treatment *		X	X
Adverse events **		X	X

* If applicable. ** Adverse events (up to 30 days after the final treatment with rivaroxaban or until end of observation); (X) if applicable/available.

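### Data collection for patients who stop rivaroxaban early appears to end at 30 days, yet both primary endpoints are reported as one-year proportions that would count the unobserved months as event-free

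*Protocol article*

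**What the plan says.** All references are to the protocol article.

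- **Horizon (2.5).** "The primary effectiveness endpoint is a composite of the following events at one year". Major bleeding, the primary safety endpoint, is also counted over one year.
- **Collection (2.6).** Endpoints are said to be recorded at 3 months and at 1 year. Final data collection is by visit or telephone at one year, with a 30-day window either way, but an exception is attached: "or at 30 days in case of an early discontinuation of rivaroxaban therapy". The sentence does not say 30 days after what.
- **After stopping (2.6).** For patients who permanently stop the combination or either drug, and who neither withdraw consent nor die, "the treating physician collects information on their survival status at the end of the study". No other item is named for that contact.
- **Table 3 footnote.** "Adverse events (up to 30 days after the final treatment with rivaroxaban or until end of observation"). This suggests that the 30 days run from the last rivaroxaban dose.
- **Analysis (2.8).** All analyses use the total study population. On the time span: "The study period for analyses is defined as the time from the start of rivaroxaban until the end of the 1-year follow-up". On the form of the results: "Incidence proportions are computed together with corresponding exact 95% confidence intervals (CIs) for primary and secondary endpoints". Follow-up ends at first event, loss to follow-up or the end of the year; stopping treatment is not on that list. The same section censors event-free patients when their individual observation ends, or at last contact, and names treatment discontinuation as one cause of missing data.

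**The concern.** A one-year proportion with every patient in the denominator requires every patient to be observed for the endpoint for one year. If discontinuers are observed only until about 30 days after stopping, their remaining months enter as event-free without having been looked at.

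Follow-up would also differ by component. Vital status is sought to one year; MI, stroke, revascularization, stent thrombosis and non-fatal bleeding are not. A late death could then enter the composite, if its cause is obtained, while a late MI in the same patient could not.

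In a single-arm registry the absolute rate is the main result, and the Discussion intends to set it against COMPASS. A rate that is low because of incomplete observation could be read as good performance.

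**Working it through.** The article gives no discontinuation rate, timing or risk after stopping, and no precision figure, so there is no stated number to reproduce. It does give N = 1000 and expected endpoint rates of 1% to 5% (2.4). All other inputs below are assumptions. Both models use constant hazards, treat 30 days as one month, and treat every event after that window as unseen.

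**Model A: stopping spread evenly over the year, hazard unchanged.** True one-year risk p = 5%, so λ = −ln(0.95)/12 = 0.00427 per month. A patient stopping at month T is observed to min(12, T + 1), on average 6.96 months. Averaging 1 − exp(−λ × observed time) over T gives 2.92% seen among discontinuers. With share d stopping, the reported proportion is (1 − d) × 5.00% + d × 2.92%:

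| d | Proportion | Relative shortfall |
|---|---|---|
| 5% | 4.90% | 2.1% |
| 10% | 4.79% | 4.2% |
| 20% | 4.58% | 8.3% |
| 30% | 4.38% | 12.5% |

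The relative shortfalls are nearly the same at p = 1% and 3%.

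**Model B: all stopping at month 4, hazard multiplied by m afterwards.** On-treatment one-year risk is 4%, so h = −ln(0.96)/12 = 0.00340 per month. Share q stops and is observed to month 5.

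- True risk = (1 − q) × 4% + q × [1 − exp(−(4 + 8m)h)]
- Proportion = (1 − q) × 4% + q × [1 − exp(−(4 + m)h)]
- Kaplan-Meier censored at month 5 = 1 − exp(−4h) × [(1 − q)exp(−h) + q exp(−mh)] × exp(−7h)

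Worked case q = 20%, m = 3: discontinuers' true risk is 9.09%, of which 2.35% is seen. True = 0.8 × 4.00 + 0.2 × 9.09 = 5.02%. Proportion = 0.8 × 4.00 + 0.2 × 2.35 = 3.67%.

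| q | m | True | Proportion | Censored Kaplan-Meier |
|---|---|---|---|---|
| 10% | 1 | 4.00% | 3.77% (5.8% low) | 4.00% (no bias) |
| 10% | 3 | 4.51% | 3.84% (14.9% low) | 4.07% (9.8% low) |
| 20% | 0.5 | 3.74% | 3.50% (6.2% low) | 3.97% (6.2% high) |
| 20% | 1 | 4.00% | 3.54% (11.6% low) | 4.00% (no bias) |
| 20% | 3 | 5.02% | 3.67% (26.8% low) | 4.13% (17.7% low) |

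**Which date counts as last contact.** Simulation of 1,000,000 patients (p = 5%, 20% stopping evenly over the year):

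| Hazard after stopping | True | Kaplan-Meier censored one month after stopping | Kaplan-Meier carried to month 12 |
|---|---|---|---|
| Unchanged | 5.00% | 4.99% | 4.57% |
| Doubled | 5.48% | 5.09% | 4.67% |

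Carrying discontinuers to the survival contact gives Kaplan-Meier the same shortfall as the proportion.

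**Against sampling error.** At 4% and N = 1000 the exact 95% interval is 2.87% to 5.41%. The Model B shortfall is 0.23 to 0.46 percentage points at m = 1, and 1.35 points at q = 20%, m = 3. The interval does not allow for this bias.

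**The case against.** The strongest reply is that the article may not truncate endpoint collection at all. Section 2.6 says without qualification that endpoints are recorded at one year. Its listed reasons for premature study termination do not include stopping treatment. The survival sentence does not contain the word only, and it also covers patients who stop aspirin alone, to whom the 30-day clause does not apply. The Table 3 footnote belongs to the adverse-event row; the clinical-outcomes row carries no 30-day limit. This stands in part: the text conflicts with itself, and the bias is conditional on truncation. But the 30-day clause is explicit, and a separate survival check would be redundant if discontinuers had full one-year endpoint collection.

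Several stronger readings are tempting but not supported:

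- **That the analysis section ignores discontinuation.** It names it as a cause of missing data and censors at the end of individual observation or at last contact. What remains is ambiguity: the list of follow-up ends omits discontinuation, and the one-year survival contact could be taken as last contact. Section 2.4 also plans a comparison of complete with incomplete follow-up, which describes the problem without correcting it.
- **That Kaplan-Meier must understate.** Properly censored, it is unbiased at unchanged hazard and runs high if risk falls after stopping, as bleeding risk may.
- **That cardiovascular death is followed to one year.** Survival status alone gives no cause of death.
- **That discontinuers are dropped from the primary analyses as incomplete cases.** "For other outcome measures, complete-case analysis will be the primary analytic approach"; this follows the time-to-event rule, and extending it to the primary endpoints is only one reading.
- **That patients who stop because of a major bleed lose safety information.** They have already had their first safety event; for them the lost time matters mainly for the ischemic composite.

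The analyses are descriptive, and the SAP is not shown. Neither point settles the matter, since the conflict is between sentences in the article and concerns its main descriptive result.

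**Conclusion.** The concern holds in conditional form. If endpoint collection is truncated as section 2.6 writes it, the full-denominator one-year proportion is biased low for both primary endpoints. Kaplan-Meier is equally low if discontinuers are carried to the survival contact. If they are censored when endpoint observation ends, it is unbiased only when stopping is unrelated to later risk; otherwise it may be low for ischemic events or high for bleeding.

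The size cannot be fixed from the article. The relative shortfall in the proportion is about 2% to 12.5% under Model A and 6% to 27% under Model B with m from 1 to 3. The upper end needs 20% stopping, all at month 4, with tripled hazard, and should not be quoted without those conditions. For the composite the shortfall would be smaller if late cardiovascular deaths are identified and counted, at the price of unequal follow-up across components.

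**What to change.** Reconcile sections 2.5, 2.6 and 2.8 with the Table 3 footnote: state what the 30 days run from, and one date at which endpoint observation ends for a discontinuer.

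1. **Where sites can still be queried:** use the one-year survival contact to record all endpoint components, including cause of death and major bleeding, to day 365. Make that the primary one-year estimate.
2. **Otherwise:** label the estimate as on-treatment. Censor all components at the same end-of-endpoint-observation date, not at the survival contact. Report Kaplan-Meier or cumulative incidence instead of the full-denominator proportion, and report one-year mortality separately. Add a sensitivity analysis for informative censoring, for example inverse-probability-of-censoring weighting; its details can sit in the SAP.

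The cost is revised wording, some programming and, for the first option, one chart query per discontinued patient at a contact that sites already make. The estimates may become slightly wider and possibly less favourable.

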### 2.7. Data Management and Source Verification

The investigator or designated authorized site personnel will enter all clinical data anonymously in an electronic case report from (e-CRF) called eDREAM (Diagram BV, Zwolle, The Netherlands; version 1.0). This e-CRF is a secure, password-protected database that is backed up frequently. The structure of the CRF is available upon request.

The clinical research organization (CRO) performs data source verification through monitoring procedures. Physical monitoring visits were performed to ensure that written informed consent, adverse vents, and data accuracy were properly documented and available. This approach was selected to balance effective monitoring with feasibility and safety considerations.

### 2.8. Data Analysis

All statistical analyses were performed using IBM SPSS Statistics, version 28.0 (IBM Corp., Armonk, NY, USA).

The statistical analyses are explorative and descriptive. All analyses are performed for the total study population (overall analyses). The study period for analyses is defined as the time from the start of rivaroxaban until the end of the 1-year follow-up.

Descriptive statistics are performed for both primary and secondary study parameters. Continuous variables are expressed as mean ± standard deviation and as medians with minimum, maximum, 25th, and 75th percentiles. Categorical variables are presented by frequency tables (absolute and relative frequencies). Incidence proportions are computed together with corresponding exact 95% confidence intervals (CIs) for primary and secondary endpoints. Cumulative incidence of events or survival probabilities and 95% confidence intervals are estimated using Kaplan–Meier estimates for primary and secondary endpoints. The follow-up starts per definition on the date of the start of treatment and ends at the date of a first event, date of loss to follow-up, or date of end of the one-year study period, whichever comes first. The incidence of events over time is studied with the use of Kaplan–Meier methods. Patients who do not experience an event of interest by the end of their individual observation period are censored.

To control for confounding, the primary analyses will employ multivariable Cox proportional hazards regression models, with adjustment for prespecified baseline covariates known to influence clinical outcomes: age, sex, presence of diabetes mellitus, renal function, and CHA_2_DS_2_-VASc score. Model assumptions, including proportional hazards, will be assessed using Schoenfeld residuals. In addition, propensity score methods will be implemented as sensitivity analyses to further address confounding and potential selection bias. Propensity scores will be estimated using logistic regression models including the aforementioned covariates. These scores will be incorporated via adjustment for the propensity score as a covariate in the Cox model.

Missing data will be categorized by cause (e.g., treatment discontinuation, withdrawal of consent, or loss to follow-up) and described in detail. For time-to-event analyses (e.g., Kaplan–Meier estimation), patients will be right-censored at the date of last contact if no event has occurred. Dropouts due to reasons unrelated to outcome (e.g., relocation or administrative issues) will be assumed non-informative.

For other outcome measures, complete-case analysis will be the primary analytic approach. In addition, we will perform sensitivity analyses using multiple imputation under the assumption of missing at random, where appropriate. This approach allows us to explore the robustness of our findings and assess potential bias due to missing data. The dropout rate and its potential effect on external validity will be reported and discussed as part of the study limitations.

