### 2.4. Study Size

The DUTCH CCS registry is a prospective, observational, single-arm study designed for descriptive and exploratory analysis. The study aims to enroll 1000 patients with chronic coronary syndrome (CCS), treated with low-dose rivaroxaban in addition to aspirin. The target sample size reflects a balance between feasibility and the goal of generating clinically meaningful insights within the study’s timeframe. Enrollment will continue beyond 1000 patients if needed to compensate for a dropout rate exceeding 5%, ensuring that sufficient patients are available for 12-month follow-up.

Although no formal power calculation was performed, the sample size is expected to provide adequate precision to estimate event rates for major outcomes, including MACEs and major bleeding, with 95% confidence intervals. Expected event rates were informed by incidence proportions observed in the COMPASS trial. However, due to the shorter follow-up period in our study (12 months vs. 23 months in COMPASS), the incidence of similar endpoints is expected to be lower. Conversely, the broader definition of clinical outcomes in our registry—which includes not only conventional MACEs but also clinically indicated coronary, peripheral, or carotid revascularization and stent thrombosis—may lead to higher overall event rates.

Furthermore, although the patient population largely resembles that of COMPASS, we include patients with higher CHA_2_DS_2_-VASc scores, potentially increasing the observed number of ischemic events. Based on these factors, we estimate that most clinical endpoints will occur in 1% to 5% of patients, which allows for reasonably precise estimates of outcome frequencies in relevant subgroups.

To support interpretation and assess the robustness of our findings, we will conduct sensitivity analyses. These include stratified analyses by clinical risk factors (such as diabetes, PAD, or prior MI), comparisons based on narrow versus broader endpoint definitions, evaluation of patients with complete versus incomplete follow-up, and exploration of site-level variability. These analyses will contextualize the observed outcomes and help determine the consistency of results across different analytical assumptions, despite the absence of formal hypothesis testing.

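### Kaplan–Meier with non-qualifying deaths censored slightly overstates the one-year absolute risks; a competing-risks estimator would remove the bias cheaply

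*Protocol article*

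**What the plan says.** The estimator is fixed in section 2.8 (Data Analysis): "Cumulative incidence of events or survival probabilities and 95% confidence intervals are estimated using Kaplan–Meier estimates for primary and secondary endpoints". The same section adds that "Patients who do not experience an event of interest by the end of their individual observation period are censored", and its paragraph on missing data repeats that "patients will be right-censored at the date of last contact if no event has occurred". Follow-up "ends at the date of a first event, date of loss to follow-up, or date of end of the one-year study period", whichever comes first. Death without an endpoint is not in that list.

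Section 2.6 does treat death as an end of observation: "Potential reasons for premature study termination include consent withdrawal, loss to follow-up, or death of the patient".

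Section 2.5 determines which deaths are events. Within the primary effectiveness endpoint, MACE is a "composite of cardiovascular death, myocardial infarction (MI), or stroke", so non-cardiovascular death is not an event. Major bleeding is a "composite of (1) fatal bleeding, (2) symptomatic bleeding into a critical organ" or bleeding that meets a hemoglobin or transfusion criterion, so a death from any other cause is not an event. The secondary endpoints are cardiovascular death and single events: MI, stroke, each type of revascularization, and minor bleeding.

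Section 2.8 also plans crude incidence proportions with exact 95% confidence intervals for the same endpoints, and multivariable Cox models. Competing risks are not mentioned anywhere.

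**The concern.** One minus Kaplan–Meier equals the cumulative incidence only if a censored patient could still have the event later. A dead patient cannot. When deaths that are not events are censored, the estimator redistributes their weight to the survivors and answers a hypothetical question: what the risk would be if nobody died of other causes. Section 2.8 calls the target the cumulative incidence of events, which is the real-world quantity, so the estimator and the named target do not match.

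The plan's own assumption about censoring does not cover this case. Section 2.8 takes censoring as non-informative for dropouts unrelated to outcome, such as relocation or administrative reasons. A cardiovascular death that is censored in the MI, stroke or revascularization curve is not of that kind.

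The silence about death in the list of follow-up ends adds an ambiguity. One analyst might censor at the date of death or at last contact. Another might carry the patient event-free to the end of the year. These choices give different curves.

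At stake are the one-year absolute risks, which are the central descriptive result of a single-arm registry and which section 4 intends to contrast with COMPASS. The error has a known direction: upward, for ischemic and bleeding endpoints alike.

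**Working it through.** **Does the text censor non-qualifying deaths?** No sentence says so directly. It follows from three statements read together: anyone without the event is censored at the end of individual observation (2.8), death ends observation (2.6), and only some deaths are events (2.5). By endpoint, the deaths that are censored are:

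- primary composite and cardiovascular death: non-cardiovascular deaths;
- major bleeding: deaths other than fatal bleeding, without an earlier major bleed;
- MI, stroke, revascularization and minor bleeding: deaths without an earlier event of that type.

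**How large is the effect?** The article gives no figure that depends on this choice, so there is nothing to reproduce.

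Inputs:

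- Event risk *p*: 1% to 5%, from section 2.4 ("we estimate that most clinical endpoints will occur in 1% to 5% of patients").
- Sample size *n*: 1000, from section 2.4.
- Competing mortality *q* over one year: not given; assumed 0.5% to 5%.

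Assume constant cause-specific hazards over the year, with *p* and *q* the true cumulative incidences of the event and of competing death. Then:

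- total hazard: H = −ln(1 − p − q);
- event hazard: h = H × p/(p + q);
- value to which 1 minus Kaplan–Meier converges: 1 − exp(−h).

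The Aalen–Johansen estimator converges to *p* itself.

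Worked case, p = 5%, q = 5%: H = −ln(0.90) = 0.10536; h = 0.10536 × 0.5 = 0.05268; 1 − exp(−0.05268) = 5.13%. The excess is 0.13 percentage points.

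| True risk p | 1 − KM, q = 0.5% | 1 − KM, q = 2% | 1 − KM, q = 5% |
|---|---|---|---|
| 1% | 1.0025% | 1.010% | 1.026% |
| 3% | 3.008% | 3.031% | 3.078% |
| 5% | 5.013% | 5.052% | 5.132% |

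The excess runs from 0.0025 (about 0.003) to 0.13 percentage points. In relative terms it is about q/2, that is 0.25% to 2.6%.

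Taken the other way, start from a Kaplan–Meier risk of 5.0% and let competing death have a net one-year risk of 1%, 3% or 5%. With h = −ln(0.95) and d = −ln(1 − competing risk), the true cumulative incidence is h/(h + d) × [1 − exp(−(h + d))] = 4.98%, 4.93% or 4.88%.

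**Against sampling error.** With 50 events in 1000 patients the exact 95% interval is 3.73% to 6.54%. The approximate half-width is 1.96 × √(0.05 × 0.95/1000) = 1.35 percentage points. The largest excess is 0.1317/1.35, or about 10% of it. For p = 1% and q = 0.5% the ratio is 0.4%.

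**The case against.** The strongest objection is size. The largest excess, 0.13 percentage points, is 0.0013 × 1000 = 1.3 patients in the whole registry. The analyses are described as exploratory and descriptive, without formal hypothesis testing, so no decision threshold can be crossed. The upper end of the assumed mortality is also doubtful for the composite, where only non-cardiovascular death competes: Table 1 excludes active malignancy, eGFR below 30 or dialysis, and Child-Pugh B or C liver failure with coagulopathy, among others. All of this stands, and it makes the point one of low severity.

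A second objection is that the plan already reports crude incidence proportions, which censoring of deaths does not inflate. That stands too, but those proportions do not account for loss to follow-up and so do not replace a correct time-to-event estimate. A difference between the two would not in itself show a defect, since Aalen–Johansen also differs from the crude proportion when patients are lost.

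A third is that a condensed article may leave the handling of death to the full protocol or SAP. That is fair for the missing entry in the list of follow-up ends. It does not cover the estimator, which the article states.

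A reader might infer more than the document supports:

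- **That absolute risks are the registry's only output.** Section 2.8 also plans Cox models, and section 2.4 plans stratified and site-level analyses.
- **That any death competes with every endpoint.** Fatal bleeding is itself a major bleeding event, and a death after an already counted MI or stroke does not compete with that endpoint.
- **That the bias will be large in elderly strata or over longer follow-up.** Section 2.4 names no age stratum, and section 4 mentions longer follow-up only as a possibility for future iterations.

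**Conclusion.** The point holds as a low-severity improvement. Applied as written, section 2.8 censors non-qualifying deaths, and 1 minus Kaplan–Meier then overstates the one-year cumulative incidence of the endpoints. The direction is certain wherever such deaths occur. The size is about 0.003 to 0.13 percentage points at the article's 1% to 5% event rates.

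That range rests on two assumptions: one-year competing mortality of 0.5% to 5%, for which the article gives no figure, and constant hazards. Within it, the bias is at most about a tenth of the confidence interval half-width with 1000 patients. It would not change the clinical reading of the results. The case for acting is that the remedy is simple and gives the quantity the article names.

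**What to change.** In section 2.8, or in the SAP:

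1. Estimate one-year cumulative incidence with the Aalen–Johansen estimator and a 95% confidence interval for each primary and secondary endpoint.
2. Name the competing event for each: non-cardiovascular death for the composite and for cardiovascular death; death other than fatal bleeding for major bleeding; death without an earlier event of that type for MI, stroke, revascularization and minor bleeding.
3. Add the date of death to the list of follow-up ends.
4. Label hazard ratios from the Cox models as cause-specific.

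The crude proportions can stay as a supplement. The cost is a few sentences and some extra analysis work, or another package if SPSS version 28 does not provide the estimator. No new data are needed: section 2.6 already records death as a reason for ending the study, and section 2.5 already calls for dates of cardiovascular death and of the other secondary events. The date of a non-cardiovascular death should be confirmed as recorded.
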